### **4.3 Determining Eligibility**

Evaluations to determine eligibility will be reviewed within 15 days prior to study entry unless otherwise specified. Referring doctors will use data from normal hospital admission tests and medical history to evaluate potential eligibility of patients. Doctors in the hospital will invite potentially eligible patients to participate.

### **4.4 Consent Methodology**

Consent will be obtained prior to any additional testing or sample collection needed for the study. For women of childbearing potential, a urine pregnancy test will be performed prior to the other laboratory evaluations. The consent forms will be prepared in Korean and back translated into English to check the content. As the majority of the patient populations from which the study subjects are drawn are literate, written consent will be obtained. Oral consent will be obtained in the case of illiterate or blind/vision disturbed subjects with the written consent being presented orally by the investigator (principal investigator or subinvestigator) and witnessed by an impartial third party. The subject will be asked to sign the form or thumb-print the form if unable to sign. A witness signature and date is only required for subjects who are presented the consent orally. The Investigator (principal investigator or subinvestigator), a trained member of the study team, will sign the form also. A copy of the consent form will be given to the subject. Consent forms will be stored in the subject study binders containing the case report forms.

### **4.5 Randomization**

Subjects will be assigned to one of the 5 drug administration times by simple randomization. A single balanced list of ID numbers with the 5 drug dose times permuted randomly across the IDs will be provided by the statistician. S/he will provide the randomized list to the centralized monitoring organization who will manage the randomization assignments for the 3 active sites. Each time a subject consents and is enrolled, a designee at that site will contact the monitoring organization who will then assign the study ID and drug dosing time for the subject by assigning the next available ID on the list.

### **4.6 Withdrawal**

Subjects who are consented to participate in the study and do not follow through with surgery, are found to be ineligible after signing the consent form, do not have an evaluable primary endpoint or request to be withdrawn will be withdrawn from the study. If the investigator believes that the study is no longer in the best interest of the subject, the subject may also be withdrawn from the study at the investigator's discretion. If possible, subjects who are withdrawn will be replaced.

### **4.7 Study Completion**

A subject will have completed the study 48 hours post surgery (vessel ligation). If a subject withdraws or is withdrawn, for any reason, before lung tissue has been transferred to the dissection team, his/her participation in the study will be completed.

## 5 An Analysis of the Study---Statistical Methods and Justification

### 5.1 Definition of Terms and PK Parameters Used in Primary and Secondary Endpoints, and in Statistical Analysis

In this study, the primary endpoint will be the relative **permeability coefficient** (*P*) of the two primary study drugs, rifampicin (RIF) and kanamycin (KM) in large necrotic nodules.

Permeability coefficient (*P*): the speed at which a compound moves through a tissue, generally due to diffusion but also to facilitated transport. Its units are cm/sec. In this study, the parameter to be determined for the rate of penetration of a drug to the lesions will be a combination permeability-surface area (**PS**) coefficient. This combined parameter is a flow, its units are cm^2.cm/sec or volume/time, but it can also be thought of as a diffusion-length term (cm^2s.cm).

Relative permeability coefficient: the ratio of the permeability coefficient for diseased tissue over that for healthy tissue. Due to the limited tissue samples that will be available for estimating permeability, we will pool the tissue data for all subjects within a single drug group to determine the relative permeability of drug to diseased nodules versus healthy lung tissue. This will allow us to work with all the tissue samples for a given subject group to simultaneously model the permeability data. By assessing its relative value to healthy tissue, it decreases the dimensionality of the model and thus will help to obtain better estimates with limited data.

Diffusion rate constant: the constant which links the change of drug concentration over time to the concentration gradient according to the following equation:

$$dC_{\text{lesion}}(t)/dt = k_{12} \cdot [C_{\text{plasma}}(t) - C_{\text{lesion}}(t)] - k_{21} \cdot [C_{\text{lesion}}(t) - C_{\text{plasma}}(t)]$$

***k*12**: diffusion rate constant from blood (compartment 1) to lesion (compartment 2);

***k*21**: diffusion rate constant from lesion to blood.

The diffusion rate constant is a function of the permeability coefficient:

$$k_{12} = PS/V_1 \quad k_{21} = PS/V_2$$

where *V*1 and *V*2 are the volumes of the two interconnected compartments (to be estimated from the drug concentration profiles in plasma and lesions).

Penetration ratio: the ratio between the area under the concentration-time curve in lesion and in blood or **AUClesion : AUCplasma** [51], where AUC is Area Under the Curve.

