#### ***Dissection of nodules and cavities from resected lung tissue***

The dissection of resected tissue will follow established SOPs for determination of drug concentration in lesions and is described here briefly. All specimen collection tubes are prelabeled and weighed to speed the dissection process.

Prior to surgery, the CT will be reviewed by the pathologist and study team to form a dissection plan. Classes of tissue to be specifically collected are: 1) several regions of apparently normal tissue, 2) large caseous tuberculomas ( $\geq 0.5$  cm), 3) cavity contents, 4) cavity walls including fibrotic tissue layer 6) fibrotic granulomas, and 7) small nodules.

Each lesion collected will be classified, measured for size (length, thickness and depth will be recorded in order to calculate surface-to-volume ratio for PK modeling) and pH, weighed, and recorded on the dissection log describing the disposition of the tissue. All lesions will be divided in this priority as follows and described in the dissection SOP.

- 1) Tissue frozen in liquid nitrogen or dry ice for drug extraction

- 2) Tissue frozen in liquid nitrogen vapor on tissue trays for Imaging Mass Spectrometry and histology
- 3) Tissue in formalin fixation solution for histology
- 4) Any remaining tissue frozen in liquid nitrogen for back-up

All lesions will have at least one sample that may be examined by normal histology methods, including hematoxylin and eosin staining of either formalin fixed or frozen sections. In addition, sections will be stained for acid fast bacilli and CD31 or CD34 (vessels). Larger lesions (0.8 cm or greater) will provide tissue for assessment of bacterial burden, bacterial genome equivalence, bacterial gene expression, and lesion cellular content using standard laboratory procedures.

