The PK/PD parameter driving aminoglycoside efficacy is the ratio between peak concentration and MIC ( $C_{\max}/\text{MIC}$ ), with a maximum effect at  $C_{\max}/\text{MIC}$  around 10-12. Aminoglycosides have a long post-antibiotic effect, which can be described as an ability to inhibit bacterial growth well after the plasma/tissue levels have fallen below the MIC.

**Moxifloxacin (MXF)** is a synthetic fluoroquinolone antibiotic. It inhibits bacterial topoisomerase II (DNA gyrase) and topoisomerase IV, which are essential enzymes playing a crucial role in the replication and repair of bacterial DNA. Its MIC, MBC and intracellular activity against MTB are 0.5, 2 and 1  $\mu\text{g/mL}$ , respectively, with again a low MBC/MIC ratio.

Moxifloxacin is used to treat a variety of respiratory infections, as well as skin and skin structure infections. Moxifloxacin is also used for the treatment of complicated intra-abdominal infection. The usual dosage is 400 mg daily taken orally or via intravenous infusion over 1 hour. Although it is increasingly used as second line agent in MDR-TB cases, the drug is not formally approved by the MFDS or the USFDA for use against pulmonary TB.

MXF is rapidly absorbed following oral administration, reaching a mean peak drug plasma concentration within 2 h after a 400 mg dose. The rate and extent of absorption are not significantly affected by food. Moxifloxacin binds weakly to plasma proteins and penetrates well into most tissue and fluid compartments, with generally higher drug concentrations in tissues than in plasma, and good intracellular penetration [3, 48]. Of the various fluoroquinolones considered for the treatment of tuberculosis, MXF exhibits the highest ELF:plasma ratio with a value of ~6 and a 20 to 70-fold accumulation in alveolar macrophages [49].

Moxifloxacin undergoes phase II metabolism in the liver to produce sulphate and glucuronide conjugates. Induction of conjugative enzymes by RIF has not been thoroughly investigated but some effect on MXF metabolism cannot be excluded since RIF was shown to induce sulphate conjugation of one oral contraceptive [50].

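### The lesion uptake equation in Protocol Section 5.1 reduces to one rate constant with no partition term, so it caps tissue:plasma exposure at 1 and cannot separate PS from V2

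*Protocol*

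**What the plan says.** Protocol Section 5.1 lists the parameters behind the primary and secondary endpoints and the statistical analysis. The penetration parameter to be determined "will be a combination permeability-surface area (PS) coefficient". The diffusion rate constant is "the constant which links the change of drug concentration over time to the concentration gradient according to the following equation". Writing Cp for plasma and Cl for lesion concentration, the equation is:

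dCl/dt = k12(Cp − Cl) − k21(Cl − Cp), with k12 = PS/V1 and k21 = PS/V2.

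The text labels k12 as blood to lesion and k21 as lesion to blood. V1 and V2 "are the volumes of the two interconnected compartments (to be estimated from the drug concentration profiles in plasma and lesions".

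Other sections that bear on this:

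- Section 3.4.2 (dissection) says that lesion "length, thickness and depth will be recorded in order to calculate surface-to-volume ratio for PK modeling".
- Section 4.5 (Study Agents) describes moxifloxacin "with generally higher drug concentrations in tissues than in plasma", and adds that "MXF exhibits the highest ELF:plasma ratio with a value of ~6".
- Section 5.4.1 takes the primary relative permeability from population PK model estimates. Section 5.4.2 obtains intervals for the AUC ratios by simulating from that model.
- Secondary endpoints 3 and 4 (Section 5.3.3) compare AUC0-24 between lesion, uninvolved lung and plasma.

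**The concern.** The two terms on the right side are the same concentration difference with the sign reversed twice. The equation therefore does not describe separate inward and outward rates. It says that tissue moves towards the plasma concentration itself, at a single speed. A real drug can settle in tissue above or below plasma. That extent (partition) is distinct from the speed of entry, and the printed form has no parameter for it.

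This is the only structural lesion model in the protocol, and it stands in the section that defines the endpoint parameters. If it is fitted, a low or high extent of distribution has to be absorbed by the rate. The exposure ratios are then bounded by the equation and not learned from the data.

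**Working it through.** **Inputs.** The equation, the definitions of k12 and k21 and the source of V1 and V2 come from Section 5.1. The design times of 2, 4, 8, 12 and 24 h come from Section 3.3. The documents give no plasma curves or lesion partitions, so the values marked as assumed below are illustrative.

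**1. The plan's own figure.** The only related computed figure is the sample size in Section 5.2. With means 1 and 0.5, SDs 0.5 and 0.25 and zero correlation, the SD of the difference is √(0.25 + 0.0625) = 0.559, so d = 0.5/0.559 = 0.894. A paired t-test with n = 12 has power 0.805, and 12/0.8 = 15. The figure reproduces and is not affected by this point.

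**2. Collapse.** Since −(Cl − Cp) = +(Cp − Cl), the right side is (k12 + k21)(Cp − Cl) = K(Cp − Cl). Solving it with (k12, k21) = (0.1, 0.4) and with (0.4, 0.1) gives identical curves (maximum difference 0).

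**3. PS and V2.** K = PS(1/V1 + 1/V2), so lesion concentrations identify K only. With K = 0.3/h and an assumed V1 of 20 L, these pairs all give the same lesion curve:

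| V2 (mL) | PS (mL/h) |
|---|---|
| 0.5 | 0.15 |
| 1 | 0.30 |
| 5 | 1.50 |
| 50 | 14.96 |

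The extra PS/V1 term is itself negligible: it multiplies K by 1 + V2/V1, which is 1.0025 at 50 mL.

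**4. The cap on exposure.** Integrating over 0 to 24 h gives Cl(24) − Cl(0) = K(AUCp − AUCl). With Cl(0) = 0:

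AUCl/AUCp = 1 − Cl(24)/(K·AUCp) ≤ 1.

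Assumed plasma curves (ka 1.5/h; ke 0.1 or 0.25/h) with K from 0.02 to 10/h give ratios of 0.27 to 0.999 and 0.32 to 0.9999. None exceeds 1. The same holds for lung:plasma if uninvolved lung is modelled by the same form. The cap needs a zero baseline. With a starting lesion level of 0.3 (on the scale of the unit-dose plasma curve) and K = 0.05/h, the ratio is 0.99 for ke 0.1 and 1.66 for ke 0.25.

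**5. Refits to data with a known partition R.** Data were generated noise-free at the five design times with true efflux rates of 0.1, 0.3 and 1/h and the plasma curves of step 4. The printed equation was then fitted on the log scale.

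| True R | True AUC0-24 ratio | Fitted ratio |
|---|---|---|
| 0.3 | 0.22–0.30 | 0.27–1.00 |
| 1 | no distortion | no distortion |
| 2 | 1.50–2.00 | 0.89–1.00 |
| 6 | 4.50–5.99 | 0.93–0.99 |

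Natural-scale fits with slightly different assumed curves (ka 1/h, half-life 2.5 to 4 h) show the same for R = 2: true 1.61–2.00, fitted 0.96–1.00. The cap does not depend on the fitting scale. The fitted rate does: across the log-scale refits, fitted K over true efflux rate ran from 0.06 to more than 20.

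**The case against.** **The equation is a definition, and the fitted model may differ.** It stands under definitions, and the separate labels for k12 and k21 suggest a slip in notation. The population model may be set out correctly in an analysis plan that is not shown. This stands as a condition: the effect on results depends on this equation being fitted. It does not make the printed rule right, and the protocol offers no other.

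**Lesion geometry is recorded.** Section 3.4.2 collects dimensions for a surface-to-volume ratio, which would give P from K. This partly answers the PS/V2 problem, but Section 5.1 says that the volumes come from the concentration profiles. Measured geometry also does not supply a partition term.

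**The moxifloxacin evidence is not about the primary pair.** The ratio of about 6 refers to lining fluid, and moxifloxacin is not in the primary comparison. Section 4.5 puts kanamycin's lining fluid:plasma ratio below 1, which does not conflict with the cap. That is correct.

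**A reader might infer that the primary contrast is wrong by a large, known factor.** On the natural scale (ka 1/h, half-life 2.5 to 4 h), a true rate of 0.3/h with partition 0.5 is fitted as about 0.08/h, nearly fourfold low. The documents do not support carrying this over to the primary endpoint, for three reasons:

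- It is a single-tissue rate, whereas the endpoint is nodule over uninvolved lung within each drug. If both tissues share a partition between 0.5 and 2, natural-scale fits return a true ratio of 0.50 as 0.43 to about 0.7, and a true ratio of 0.33 as 0.34 to 0.46. Much of the error cancels. Cancellation is poor at partition 0.3, can fail on the log scale at 0.5 or below, and is not assured when the two partitions differ.
- On the log scale, the same single-tissue case returns 0.27 to 0.37/h, close to the truth.
- The documents give no lesion partition for rifampicin or kanamycin.

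**Conclusion.** Wrong as written. Three statements follow from the printed equation without further assumption: there is one identifiable rate constant, there is no partition term, and lesion concentrations alone do not separate PS from V2.

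The cap of 1 on the tissue:plasma AUC0-24 ratio also requires that no drug is present before the dose. That holds for rifampicin, because Section 4.2.2 excludes rifamycin use in the preceding 30 days. It holds for the other drugs unless they are already in the subject's regimen, which Section 3.3 allows.

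If the equation is fitted, secondary endpoints 3 and 4 are biased for any drug and tissue whose true partition is not 1. A reader might infer that every AUC ratio is distorted. That is too broad: a partition of 1 gives no distortion, and lesion:lung ratios are not capped.

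The primary contrast is at risk of bias, chiefly when nodule and uninvolved lung have different partitions. Its size and direction depend on the error model and on partitions that the documents do not give, so no fold-error should be quoted for it.

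**What to change.** - Replace the equation by dCl/dt = kin·Cp − kout·Cl, equivalently k(R·Cp − Cl) with k = kout and R = kin/kout. Estimate R per drug and tissue.
- State which of kin and kout carries PS over volume. They differ by the factor R, so the choice changes the nodule-over-lung ratio by the ratio of the two partitions.
- Take the surface-to-volume ratio from the lesion dimensions already recorded, in place of estimating V2 from the concentration profiles.
- Derive the AUC ratios from k and R together.
- Keep the primary endpoint as relative permeability, and state how the uninvolved-lung term, which has no lesion surface, is scaled. Using bare rate constants instead would redefine the endpoint.
- Report the one-parameter model (R = 1) as a sensitivity analysis.

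**Cost.** No new samples or visits are needed, and the 12/15 sample size statement stands. The price is one extra parameter per drug and tissue. With 15 subjects, one lesion each and 50% CV, the standard error of log k with R estimated is about 0.13 to 0.46 for k between 0.05 and 0.5/h. The loss is small at 0.2/h or above. At 0.05/h it is material: if the contrast is treated as four independent estimates, power for a twofold difference falls from just under 0.6 to about 0.12–0.15. The plan should acknowledge this.

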### 5.2 Sample Size Justification

Comparison of the permeability was chosen as the primary endpoint rather than drug exposure in lesions relative to plasma. This type of endpoint is often adopted in case of sparse PK sampling design, where each subject essentially contributes plasma and tissue PK measurements at one or few time points. In such case, AUC or drug exposure over time cannot be estimated accurately but is rather fit to a model. On the other hand, since each time point/subject will contribute plasma, lung tissue and 2-5 lesion measurements, an estimation of *P* for each drug, using pooled PK data across subjects, can be made with much better precision than an estimation of AUC. Because a tissue sample will be taken from each subject only at one time point, pharmacokinetic data pooled across subjects will be used to fit a population PK model. However, for tractability, the sample size is justified by the variability expected in the individual permeability coefficient.

For any given drug, the variability of the permeability coefficient (P) across subjects or between similar lesions within one subject is expected to be around 50% or typical PK variability. The range of variation of P between drugs and lesion types is more difficult to assess. According to Sauermann et al [12], the range of P within abscesses can be as wide as 6 orders of magnitude. However, the study deals with abscesses which are widely scattered throughout the body and therefore don't have a common regional blood flow to draw from (except cardiac output). Also, since Sauermann et al [12] estimate the spatial parameters V and S and fix them in the data analysis, all the variability has to be incorporated into their estimate of P. In this study, we will have tissues from one anatomical location (lung) but of differing pathology.

The sample size for this study was determined based on the number of subjects necessary to detect a 50% difference in the individual permeability coefficient for caseous necrotic nodules between RIF and KM with 80% power. The SD of each P coefficient is assumed to be 50% the underlying population mean of P. Furthermore for the purposes of the sample size calculation, it is assumed that there is zero correlation between the 2 permeability coefficients. This assumption will be conservative so long as the coefficients for RIF and KM are not negatively correlated. With these assumptions, and normally distributed differences in the coefficient P between the 2 drugs, a paired t-test would need 12 subjects. A 20% inflation factor was applied to the sample size to allow for loss of data due to some administrative or analytical issue. The required sample size for this study is thus 15 subjects.

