## 1. Précis – Abstract

It takes 6 to 24 months of intensive combination therapy to cure tuberculosis (TB) with antibiotics that have proven activity in vitro. In contrast, many pulmonary infectious diseases can be cured following single drug treatment with similar drugs for only one to a few weeks. We hypothesize that the unusual complexity of TB lesions and the degree of sequestration of TB bacilli within these lesions may limit access of the drugs to their site of action, leading to treatment failure, long treatment duration and the emergence of drug resistance. To test the hypothesis that drug maldistribution into lesions impacts on treatment duration and failure, we propose to examine the lesion-specific penetration properties of 5 standard anti-TB drugs in the lungs of subjects selected for lung surgery. The study is designed to understand what lesion types are the most difficult to penetrate. This aspect of TB drug pharmacokinetics has been largely neglected so far, probably owing to the lack of adequate technology and the limited availability of human TB lesion samples. Fifteen patients who elect lung resection surgery will be asked to participate in the study. Consented subjects will receive 5 first and second line anti-TB drugs concomitantly at 1 of 5 pre-determined times prior to surgery. At the time of resection, drug levels will be measured in plasma, in uninvolved lung tissue and in lesions using standard analytical methods as well as imaging Mass Spectrometry (MS) where drug concentration gradients can be visualized across tissue sections. The major aim of this study is to determine actual concentrations and permeability coefficients of the 5 study drugs in various lesion types contained within subjects' surgically removed lung tissue. Data analysis will also provide the **relative exposure** of each drug in plasma versus lung tissue and lesion. If conclusive, the results may be taken into consideration when selecting drug doses and dosing regimens. Additionally, images generated by standard of care (SOC) High Resolution Computed Tomography (HRCT), and Dynamic MRI for each subject will provide information regarding lesion structure and anatomy, lesional blood flow and microvascular function. Lesion-specific correlations will be established between CT radiology and drug pharmacokinetic (PK) to identify which histopathologic lesion types may be particularly difficult to sterilize and to evaluate the potential impact of drug penetration on treatment outcome. The long term goal of this study is to identify the factors behind poor lesion penetration, so that new agents can be optimized with better penetration properties to target 'harder-to-sterilize' lesion types.

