### Doses:

- Rifampicin (RIF) will be dosed orally at 600mg or 450mg for subjects under 50kg of bodyweight;
- Isoniazid (INH) will be dosed orally at 300mg;
- Pyrazinamide (PZA) will be dosed orally at 1.5g;
- Moxifloxacin (MXF) will be dosed orally at 400mg;
- Kanamycin (KM) will be dosed intramuscularly at 1g or 750mg for subjects under 50kg of bodyweight

The 5 groups of subjects are distinguished by the timing of the drug administration, determined by randomization. The timing will be one of 24, 12, 8, 4, and 2 hours prior to estimated vessel and bronchus ligation time, which takes place at varying times after the start of surgery, depending on the extent of adhesions between the pleural membrane and the lung lobes. These times may vary slightly due to constraints inherent to the surgical procedure. Therefore, the exact timing of vessel and bronchus ligation relative to drug administration will be recorded accurately. Ligation marks the time of isolation between tissue compartment and plasma compartment, and will therefore be used as the time post-dosing in the PK analysis.

We will allow the following deviations from assigned timing between drug administration and vessel ligation:

- minus 1h and plus 3h for the 2h group
- minus 2h and plus 4h for the 4h group
- minus 4h and plus 6h for the 8h group
- plus or minus 6h for the 12h group
- plus or minus 12h for the 24h group

In cases where these maximum deviations are exceeded, samples will be collected and analyzed for drug content, but the data will be marked as falling outside allowable time points. To compensate for these potential fall-outs, enrollment will continue until evaluable tissues from 3 subjects falling within the allowable window are obtained in each group. Two statistical analyses will be conducted, one including only those subjects in compliance with the protocol, and one including all subjects. Both sets of results will be interpreted in light of the cause(s) for delay.

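### Fifteen is given as the total enrolled after a 20% loss allowance, but enrolment stays open until fifteen are evaluable, so the number enrolled is understated and has no ceiling

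*Protocol*

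**What the plan says.** Section 5.2 finds that a paired t-test needs 12 subjects, applies a 20% inflation for data lost to administrative or analytical problems, and closes with "The required sample size for this study is thus 15 subjects". The abstract gives the same total: "Fifteen patients who elect lung resection surgery will be asked to participate in the study". Section 3.3 describes five groups of three, each given one dose of the five drugs.

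Sections 3.1 and 3.3 set a different stopping rule. Section 3.3 says that "enrollment will continue until evaluable tissues from 3 subjects falling within the allowable window are obtained in each group", and section 3.1 has a similar rule for evaluable tissue at each time point. Section 4.6 withdraws, among others, subjects who "do not have an evaluable primary endpoint or request to be withdrawn will be withdrawn from the study", and adds that withdrawn subjects will be replaced if possible.

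On allocation, section 4.5 begins: "Subjects will be assigned to one of the 5 drug administration times by simple randomization". Its next sentence describes one balanced list with the five times randomly permuted over the ID numbers. Each subject who consents and is enrolled is allocated by "assigning the next available ID on the list". No separate rule for replacements is given, nor are the list length, any blocking, or an expected or maximum number enrolled.

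**The concern.** In section 5.2 and the abstract, 15 is the count before losses: 15 go in and about 12 come out usable. In the stopping rule, 15 is the count after losses: five times with three evaluable subjects each. One number is doing two jobs, and the reader cannot tell how many people will be enrolled.

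This matters because section 10.3.1 states that subjects gain no benefit from taking part. The ethics boards see fifteen, while the rule that governs recruitment implies more and sets no limit. The allocation text adds to this. If a replacement takes the next ID, it may fall at a dosing time that already has its three evaluable subjects, and enrolment must continue until the deficient time comes up again.

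**Working it through.** **Step 1. Reproduce the plan's figures.** Section 5.2 aims to "detect a 50% difference in the individual permeability coefficient for caseous necrotic nodules between RIF and KM with 80% power" and states: "The SD of each P coefficient is assumed to be 50% the underlying population mean of P". It assumes zero correlation. Two-sided alpha 0.05 is not given in 5.2; it is inferred from the 95% confidence interval rule in 5.4.1.

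- Set the means at 1 and 0.5, so the SDs are 0.5 and 0.25.
- SD of the paired difference = √(0.5² + 0.25²) = 0.559.
- Standardised effect = 0.5 / 0.559 = 0.894.
- Exact noncentral t: n = 12 gives power 80.5%; n = 15 gives 89.6%.
- Inflation: 12 / 0.8 = 15. The other common form, 12 × 1.2 = 14.4, also rounds up to 15.

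Both 12 and 15 reproduce.

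**Step 2. Apply the stopping rule.** The evaluable target is 5 × 3 = 15. With the same 20% allowance, the number to enrol is 15 / 0.8 = 18.75, about 19 (15 × 1.2 gives 18). The chance that the first 15 enrolled all prove evaluable is 0.8^15 = 3.5%.

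**Step 3. Vary the loss and the replacement rule.** The protocol gives no overall rate for unusable tissue, missed windows and withdrawal together, so 10%, 20% and 30% are assumptions. Same-time replacement has expected enrolment 15 / (1 − loss). The next-ID columns are means of 8,000 simulated enrolments each, run until every time has three evaluable subjects, with the list renewed when exhausted.

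| Assumed loss | Chance that 15 enrolled are all evaluable | Same-time replacement | Next ID, blocks of 5 | Next ID, blocks of 15 | Next ID, balanced list of 30 |
|---|---|---|---|---|---|
| 10% | 0.9^15 = 20.6% | 16.7 | 19.1 | 20.0 | 22.0 |
| 20% | 0.8^15 = 3.5% | 18.75 | 23.2 | 24.2 | 25.1 |
| 30% | 0.7^15 = 0.5% | 21.4 | 28.3 | 28.9 | 29.4 |

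The simulated 95th percentile under same-time replacement is 19, 23 and 27 at the three loss rates. At 20% loss the three next-ID schemes have 95th percentiles of 33 to 34 and end with 18.6 to 20.1 evaluable subjects on average, against a target of 15. With no loss at all, blocks of 5 or 15 stop at exactly 15, but a balanced list of 30 still averages 19.8.

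**Step 4. Compare the replacement rules.** At 20% loss, next-ID assignment costs 23.2 − 18.75 = 4.5 to 25.1 − 18.75 = 6.4 more enrolments on average than same-time replacement.

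**The case against.** The strongest defence is that two kinds of loss are in play. The 20% in section 5.2 covers administrative and analytical loss, while the open enrolment in section 3.3 compensates for missed time windows. On that reading, fifteen subjects supply in-window tissue and about twelve have usable data after the assays. This is coherent as far as it goes, but it does not rescue 15 as the number enrolled: any missed window or unusable specimen already takes enrolment above 15. Section 4.6 also blurs the split, because it replaces, if possible, subjects with no evaluable primary endpoint, whatever the cause.

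Several limits do stand. Applying 20% to all losses is an assumption. Replacement under section 4.6 is only if possible. Next-ID assignment of replacements is the natural reading of section 4.5, but the section does not mention replacements. The analysis pools subjects in a population model that uses actual ligation time, so exact balance is not critical, and surplus subjects add information. The open-ended rule is also visible in the text.

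A reader might go further in three ways that the document does not support:

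- **That the sample size calculation is wrong.** It reproduces, and the stopping rule raises power.
- **That taking simple randomization literally would push enrolment to about 32.** Simulation gives that figure at 20% loss, but the next sentence of section 4.5 describes a balanced list, so the label is at fault and the figure does not apply.
- **That data from withdrawn subjects are thrown away.** Section 4.6 says they are withdrawn, not that their data are discarded, and section 3.3 plans a second analysis of all subjects.

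**Conclusion.** The concern holds as a contradiction about the number enrolled. Fifteen is correct as an inflated sample size for 12 usable subjects, and it is also the evaluable target, but it can serve as both only if loss is zero. Expected enrolment is about 17, 19 or 21 at assumed losses of 10%, 20% or 30% with same-time replacement. If replacements follow the next-ID rule, it is about 19-22, 23-25 or 28-29. These ranges rest on independent losses at a common rate and on assumed list structures. The direction is the same in every case examined with loss above zero.

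The consequence is an understated and uncapped number of participants, not a loss of power or validity. Enrolled is also not the same as dosed, since some withdrawals occur before drug administration, so the number exposed will lie somewhat below these totals. Separately, section 4.5 contradicts itself by naming simple randomization and describing a balanced permuted list.

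**What to change.** - In section 5.2, state three numbers separately: 12 evaluable as the minimum for 80% power; 15 evaluable (three per dosing time) as the target; and the expected enrolment, about 19 at an assumed overall loss of 20%, with the assumption named.
- Add a maximum enrolment. The 95th percentile under same-time replacement, 23 at 20% loss, is one basis. Say what happens if the ceiling is reached before every time has three evaluable subjects.
- Align the abstract and the description of the groups in section 3.3 with these numbers.
- In section 4.5, replace the term simple randomization by the balanced permuted list, with its length and blocking fixed in the randomization documents.
- State that the central office assigns each replacement to the dosing time of the subject replaced.

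The cost is an amendment to the wording and one added instruction for the central office, which already controls assignment. At 20% loss, same-time replacement saves about 4.5 to 6.4 enrolments on average compared with next-ID replacement, and the evaluable target is unchanged.
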